## Abstract

**Background:**

The incidence, mortality, and prevalence of chronic obstructive pulmonary disease (COPD) are high in China. Acute exacerbations of COPD (AECOPD) are important events in the management of COPD because they negatively impact health status, rates of hospitalization and readmission, and disease progression. AECOPD have been effectively treated with Chinese medicine for a long time. The aim of this proposed trial is to assess the therapeutic effect of Chinese medicine (CM) on AECOPD.

**Methods/design:**

This proposed study is a multicenter, double-blind, parallel-group randomized controlled trial (RCT). We will randomly assign 378 participants with AECOPD into two groups in a 1:1 ratio. On the basis of health education and conventional treatment, the intervention group will be treated with CM, and the control group is given CM placebo according to CM syndrome. Patients are randomized to either receive CM or placebo, 10 g/packet, twice daily. The double-blind treatment lasts for 2 weeks and is followed up for 4 weeks. The main outcome is the COPD Assessment Test; secondary outcomes are treatment failure rate, treatment success rate, length of hospital stay, AECOPD readmission rate, intubation rate, mortality, dyspnea, the 36-item Short Form Health Survey, and the COPD patient-reported outcome scale. We will document these outcomes faithfully at the beginning of the study, 2 weeks after treatment, and at the 4 weeks follow-up.

**Discussion:**

This high-quality RCT with strict methodology and few design deficits will help to prove the effectiveness of CM for AECOPD. We hope this trial will provide useful evidence for developing a therapeutic schedule with CM for patients with AECOPD.

**Trial registration:**

ClinicalTrials.gov, NCT03428412. Registered on 4 February 2018.

## Background

Chronic obstructive pulmonary disease (COPD) is a common and frequently occurring disease that is greatly harmful to human health. It is currently the fourth leading cause of death in the world [1] but is projected to be the third leading cause of death by 2020. More than 3 million people died of COPD in 2012, accounting for 6% of all deaths globally [2].

Acute exacerbations of COPD (AECOPD) are important events in the management of COPD because they negatively impact health status, rates of hospitalization and readmission, and disease progression. Patients with COPD are susceptible to about 0.5 to 3.5 exacerbations per year. AECOPD is an important factor in the death of COPD patients. In 2013, the total number of COPD deaths in China was about 910,000 and in terms of the number of single diseases ranked No. 3; deaths from COPD accounted for 11% of all deaths in China. Note in particular that the total population with COPD in China accounts for 31.1% of the total number of COPD deaths in the world [3]. COPD is projected to be the fifth economic burden in the world by 2020 [2]. We also point out that AECOPD accounts for a major part of the medical expenses for patients with COPD. The in-hospital mortality for AECOPD was 4.3% with mean costs up to $9545 in the USA in 2006 [4]. The mean cost per admission of hospitalization in patients with AECOPD was up to CNY ¥ 11,598 in China [5]. AECOPD is an important clinical event in COPD and a major determinant of the health status and prognosis of patients with COPD. The early prevention, early detection, scientific understanding, and standardized treatment of AECOPD constitute a major and arduous medical task in clinical practice.

There is a good clinical efficacy of Chinese medicine (CM) for AECOPD patients. However, the experimental design for most clinical studies is unfeasible, the quality of randomized controlled trials (RCTs) is low, and efficacy evaluation indicators are complex and unstandardized [6]. High-quality clinical trials including a scientific design and showing reasonable outcomes on the treatment of AECOPD by CM are urgently needed. Therefore, we conducted a prospective RCT to investigate the effectiveness and safety of CM compared to conventional drugs on patients with AECOPD.

## Methods/design

### Objectives

The study objectives are as follows:
Clinical outcome: to test the clinical efficacy of CM for patients with AECOPDSafety evaluation: to evaluate the safety of CM on AECOPD patients.

### Study design

This double-blind, multicenter, parallel-group, superiority, 1:1 randomization ratio prospective clinical study was approved by the Institutional Review Board of the First Affiliated Hospital of Henan University of Chinese Medicine (reference number 2017HL-069-01, validated on 22 November 2017) and registered at ClinicalTrials.gov (NCT03428412). The protocol follows the recommendations of the Standard Protocol Items: Recommendations for Interventional Trials (SPIRIT) initiative (Additional file 1) [7].

The flowchart of the study process is detailed in Fig. 1. The timing of treatment visits and data collection is detailed in Table 1.

**Fig. 1 Fig1:**
[figure not shown]
Flowchart for the intervention trial

**Table 1 Tab1:** Timing of treatment visits and data collection

	Baseline	Treatment phase				Follow-up phase	
	Day 0	Day 4	Day 7	Day 10	Day 14	Day 28	Day 42
	V1	V2	V3	V4	V5	V6	V7
Sign informed consent	×						
Randomization	×						
Medical history	×						
Intervention	×	×	×	×			
Primary outcome							
CAT	×				×	×	×
Secondary outcomes							
Treatment failure		×	×	×	×		
Length of hospital stays					×		
Readmission due to AECOPD						×	×
Intubation rate		×	×	×	×	×	×
Mortality		×	×	×	×	×	×
mMRC	×	×	×	×	×	×	×
SF-36	×				×	×	×
COPD-PRO	×				×	×	×

### Sample size

The COPD Assessment Test (CAT) will be used as the main outcome. According to previous study results, the average CAT score of AECOPD patients treated by CM is 16.54 ± 5.50 and that of the placebo is 18.33 ± 5.87 [8]. The most reliable estimate of the minimum important difference of the CAT is 2 points [9]. Assuming that α is 0.05 and power is 90%, the two-sided *Z*
_1-α/2_ is 1.96 and *Z*
_1-_β is 1.28. The standard deviation of the first group (σ_1_) is 5.50 and that of the second group (σ_2_) is 5.78, and the clinically meaningful difference (δ) is 2. Based on the formula $$ n=\frac{{\left({{Z_{1-}}_{\alpha}}_{/2}+{Z_{1-}}_{\beta}\right)}^2\times \left({\sigma_1}^2+{\sigma_2}^2\right)}{\delta^2} $$, the sample size in each group is 170. Considering a 10% dropout rate over the course of the study, 189 patients will be enrolled in each group. The total sample size will be 378.

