### Outcomes

#### Primary outcome: COPD Assessment Test (CAT)

The primary outcome of this study will be changes in the CAT between baseline, 14 days after treatment, and the 28 and 42 days follow-ups. We will use the CAT to evaluate the impact of AECOPD on a person’s life and how this changes over time.

The CAT is an 8-item questionnaire designed to assess and quantify health-related quality of life and symptom burden in patients with COPD [10, 11]. Each questionnaire item is presented as a semantic 6-point (0–5) differential scale, providing a total score out of 40. Scores of 0–10, 11–20, 21–30, 31–40 represent mild, moderate, severe, or very severe clinical impact, respectively [12]. Evidence has shown the CAT may also prove useful in clinical trials to objectively assess the ability of novel interventions to reduce AECOPD severity [13], and it is a potentially useful instrument to assess the efficacy of treatments following COPD exacerbations [14].

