### Statistical analysis

All data will be analyzed according to the intention-to-treat (ITT) and per-protocol (PP) analyses to reduce deviation. The modified intention-to-treat (mITT) analysis set is a subset of the ITT population and allows the exclusion of some randomized subjects in a justified way. The PP analysis set will include patients who fully complete the trial. The mITT analysis set is used for efficacy and the PP analysis set for safety. Continuous variables will be presented as mean and standard deviation or median and interquartile range according to the Kolmogorov-Smirnov test, and categorical variables as number of patients and proportion.

The Student’s *t* test will be used to compare differences in measurement data. The rank sum test will be used to deal with ranked data, the chi-squared test will be used to analyze categorical data, and the repeated measures analysis of variance (ANOVA) test will be used to analyze multiple measurements at different time-point data. If the effect of the different centers is significant, the Cochran-Mantel-Haenszel (CMH) chi-square test or analysis of covariance (ANCOVA) test is used to correct it. A statistician not involved in data collection will conduct all statistical analyses using SPSS version 23.0 software (SPSS Inc., Chicago, IL, USA).

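### The 90% power is worked out for CAT scores, but the primary outcome is change in CAT and the named tests do not adjust for baseline; adjusting for baseline CAT would close the gap at no cost in patients

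*Protocol article*

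**What the plan says.** All places are in the protocol article.

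- **Sample size.** The variability comes from an earlier study's scores by arm: "the average CAT score of AECOPD patients treated by CM is 16.54 ± 5.50 and that of the placebo is 18.33 ± 5.87". The target difference rests on the statement "The most reliable estimate of the minimum important difference of the CAT is 2 points", with 90% power and two-sided α of 0.05. The result is "the sample size in each group is 170", raised to 189 per group and 378 in total for 10% dropout. When the inputs are restated for the formula, the second SD is printed differently: "that of the second group (σ_2_) is 5.78, and the clinically meaningful difference (δ) is 2".
- **Primary outcome.** "The primary outcome of this study will be changes in the CAT" between baseline and days 14, 28 and 42. Table 1 schedules CAT at day 0 and at those three visits.
- **Statistical analysis.** Student's "test will be used to compare differences in measurement data", and repeated measures ANOVA is assigned to data from several time points. ANCOVA appears once, as an alternative to the CMH test for correcting a significant centre effect. Baseline CAT is not named as a covariate.

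**The concern.** The variance of a score and the variance of a change from baseline are different quantities. They are linked by the correlation r between baseline and follow-up and by the ratio of the two SDs, and the article gives neither. A power figure computed from score SDs does not carry over to a test on changes without an assumption about both.

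If r is low, an unadjusted test on change is noisier than the calculation allows, and the trial could miss a 2-point difference more often than the stated 10% of the time. Baseline CAT is planned for every patient, so a more efficient analysis is available without collecting anything further.

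**Working it through.** **Inputs from the Sample size section:** z values 1.96 and 1.28; SDs 5.50 and 5.87 (also printed as 5.78); δ = 2; 170 per group.

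**Assumed, not in the article:** r, shown as a range, and the ratio k of baseline SD to follow-up SD, taken as 1 unless stated. The quoted score SDs are taken as follow-up SDs.

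**1. Reproduce the plan's figure.**
- With 5.87: (1.96 + 1.28)² × (5.50² + 5.87²) / 2² = 10.4976 × 64.7069 / 4 = 169.8, so 170. Then 170 / 0.9 = 188.9, so 189 per group and 378 in total.
- With 5.78: 10.4976 × 63.6584 / 4 = 167.1, so 168.

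The stated 170 follows from 5.87. The common SD is √(64.7069 / 2) = 5.69. Power at 170 per group is 90.0% with 5.87 and 90.5% with 5.78, so the misprint is minor.

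**2. Compare a change-score t test with ANCOVA at one visit.** Power = Φ(2 / (SD × √(2/170)) − 1.96), where, for k = 1:
- SD of change = 5.69 × √(2(1 − r))
- residual SD under ANCOVA = 5.69 × √(1 − r²)

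| r | SD of change | Power, t test on change | Total N for 90% on change | ANCOVA SD | Power, ANCOVA |
|---|---|---|---|---|---|
| 0 | 8.04 | 63.0% | 756 | 5.69 | 90.0% |
| 0.2 | 7.19 | 72.7% | 606 | 5.57 | 91.1% |
| 0.3 | 6.73 | 78.2% | 530 | 5.43 | 92.5% |
| 0.4 | 6.23 | 84.1% | 454 | 5.21 | 94.3% |
| 0.5 | 5.69 | 90.0% | 378 | 4.93 | 96.3% |
| 0.6 | 5.09 | 95.2% | 304 | 4.55 | 98.2% |

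**3. Unequal SDs.** The variance of change is SD² × (1 + k² − 2rk), where SD is the follow-up SD. It equals SD² when r = k/2, so the break-even is 0.4 at k = 0.8, 0.5 at k = 1 and 0.6 at k = 1.2. At r = 0.5, power on change is 94.3% at k = 0.8 and 82.9% at k = 1.2. The ANCOVA variance, SD² × (1 − r²), does not depend on k. The change-score variance exceeds it by SD² × (k − r)², which is never negative.

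**4. Other contrasts** (k = 1, the same correlation between all visits, a 2-point effect at each follow-up visit).
- Mean of three follow-ups minus baseline: variance SD² × (4/3)(1 − r), break-even r = 0.25.
- Group-by-time test over four visits: power 81.2%, 87.3% and 92.9% at r = 0.3, 0.4 and 0.5.
- t test on follow-up scores at one visit: 90.0%, as planned, whatever r is.
- Mean of the three follow-up scores: variance SD² × (1 + 2r)/3, never above SD², so power is at least 90%.

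**The case against.** The strongest reply is that the article never fixes a single-visit change-score t test for CAT. The t-test sentence can be read as covering between-group differences in any continuous variable. CAT is measured at four visits, so repeated measures ANOVA may be what is meant, and there baseline enters as one of the levels. This stands. A reader might infer that 90% power holds only if r is at least 0.5. The article does not support that, because this threshold belongs to one test with equal SDs and moves, or disappears, under the other readings.

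A reader might also infer that the trial is underpowered because baseline is taken during an exacerbation and r must therefore be low. That is plausible, but the article gives no r and no baseline SD, and the range shown runs both above and below 90%.

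The last objection is that covariates are usually left to the analysis plan, which is not shown. This stands only in part. The point is not that a covariate list is missing: the article names the tests and gives ANCOVA a conditional role tied to centre. If the analysis plan already adjusts for baseline CAT, the article's text should be reconciled with it. Neither named method is invalid in a randomized trial. The issue is efficiency, and what the 90% refers to.

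**Conclusion.** The mismatch is in the text: score SDs in the calculation, change as the outcome, and named tests without a baseline covariate. The 90% is demonstrated for a comparison of scores and not for a comparison of changes. For a change-score t test at one visit with equal SDs, power is 78% at r = 0.3 and 95% at r = 0.6, with break-even at 0.5, or at k/2 in general. A loss of power is possible but not shown.

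Baseline-adjusted analysis has no larger variance than the change-score test at any r and k. It would still be too much to say that it guarantees 90%: that holds, approximately and for a single visit, only if the follow-up SD is near 5.69 and δ is 2. The 5.87/5.78 discrepancy is a separate, minor slip and adds nothing to the main point.

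**What to change.** - **Statistical analysis:** make the primary analysis an ANCOVA or mixed model of post-baseline CAT with baseline CAT as a covariate in all cases, not conditional on a test of centre effects.
- **Sample size:** say that the SDs and the 90% power refer to a comparison of CAT scores, and print the second SD as 5.87 in both places.

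The cost is wording in the protocol and analysis plan, plus one degree of freedom. No extra patients or measurements are needed, and 378 stands under the plan's own SD and δ. The Trial status section reports recruitment as complete, so the analysis is the remaining lever. The change should be dated before CAT is compared by group, particularly because the Randomization and blinding section excepts the data analysts from blinding.

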### Randomization and blinding

A central dynamic stochastic distribution method is adopted. The randomization sequence will be generated by the ‘proc plan’ procedure of SAS software (version 23.0) according to stratified block randomization with a block size of 6, and the random number and group assignment will be obtained from a central randomization system provided by Jiangsu Famous Medical Technology Co., Ltd. in Nanjing, China. Eligible AECOPD patients will be randomly divided into an experimental group and a control group in a 1:1 allocation ratio. The data management and statistical analysis units formulate a random distribution scheme according to the test scheme. They then implement and manage the random distribution scheme through a central random distribution interactive voice operating system. The researcher obtains the subject assignment code via the Internet or phone.

All participants, trial participants, care providers, and outcome assessors except for the data analysts are blind to treatment allocation. The CM placebo packaging in the control group is consistent with the CM granules, and the odor and color are also similar to those of the experimental group CM granules, but there is no clinical effect. If serious adverse events that threaten the safety of participants occur, we will immediately stop the intervention, cancel the blinding, and contact the Institutional Review Board.

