### Data management

The Independent Data Monitoring Committee (IDMC) is a group of clinicians and biostatisticians appointed by study sponsors who provide independent assessment of the safety, scientific validity, and integrity of clinical trials [21]. The IDMC members of this study include two clinicians and one biostatistician with expertise in clinical trial and interim data analysis. The functions and frequency of its meetings are dictated by the DMC charter. The IDMC can recommend premature closure or reporting of the trial.

In order to improve patient compliance, we have taken the following measures: (1) we explain the purpose, significance, and related follow-up time of the study before enrollment; (2) we perform regular telephone follow-up to be informed of the changes in the subject’s condition and provide necessary assistance.

Jiangsu Famous Medical Technology Co., Ltd. in Nanjing, China is responsible for managing the data (e.g., plans for data entry, coding, security, and storage, double data entry; range checks for data values), formulating statistical analysis plans, writing statistical analysis reports, and final review by the project responsible unit.

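### The data analysts are declared unblinded, with no stated separation from the holders of the allocation code, while exclusions from the efficacy set rest on judgement

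*Protocol article*

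**What the plan says.** Four places in the protocol article bear on this.

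- **Randomization and blinding, who is blind:** "All participants, trial participants, care providers, and outcome assessors except for the data analysts are blind to treatment allocation". The analysts are the only group excepted.
- **Randomization and blinding, who handles the scheme:** "The data management and statistical analysis units formulate a random distribution scheme according to the test scheme". The next sentence reads: "They then implement and manage the random distribution scheme through a central random distribution interactive voice operating system". The random number and assignment come from "a central randomization system provided by Jiangsu Famous Medical Technology Co., Ltd. in Nanjing, China".
- **Data management:** "Jiangsu Famous Medical Technology Co., Ltd. in Nanjing, China is responsible for managing the data", and its duties also include "formulating statistical analysis plans, writing statistical analysis reports, and final review by the project responsible unit".
- **Statistical analysis:** "A statistician not involved in data collection will conduct all statistical analyses using SPSS version 23.0 software". Efficacy is assessed in the modified intention-to-treat (mITT) set, which "allows the exclusion of some randomized subjects in a justified way".

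The Participants section adds two grounds for rejecting a patient: a breach of the plan serious enough to affect the assessment of efficacy and safety, and data too sparse to judge either.

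**The concern.** Unblinded analysts do little harm when every decision that affects the comparison has been fixed beforehand. Here, two kinds of decision are left to judgement. One is which randomised patients may justifiably leave the mITT set; the other is which departures from the plan are serious enough for rejection. Both determine who is counted in the efficacy comparison. If the people who settle them know, or can look up, the allocation, an exclusion can be influenced by arm and outcome together, even without intent. The blinding of patients, care providers and assessors does not protect against that, because it happens after the data are in.

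The one safeguard stated for the analysis is that the statistician takes no part in data collection. That makes the statistician independent of the sites. It does not make the statistician blind.

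**Working it through.** **1. Reading the passages together.**

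| Function | Who, according to the article |
|---|---|
| Formulate, implement and manage the allocation scheme | Data management and statistical analysis units |
| Provide the central randomisation system | The contractor |
| Manage the data | The same contractor |
| Write the analysis plan and statistical reports | The same contractor, with final review by the project responsible unit |
| Run the analyses | A statistician outside data collection, affiliation not given |
| Blind status of the analysts | Not blind |
| Decide mITT exclusions and rejections | Not stated |

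The article does not expressly say that the two units belong to the contractor, but the functions named are the same. Nowhere does it separate the holders of the code from those who analyse.

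**2. The plan's own figure.** There is none on blinding. The illustration below borrows the sample-size inputs, so those were checked first, with n = (1.96 + 1.28)² × (σ₁² + σ₂²) / δ², σ₁ = 5.50 and δ = 2.

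- σ₂ = 5.78: 10.4976 × (30.25 + 33.4084) / 4 = 167.07, which rounds up to 168.
- σ₂ = 5.87: 10.4976 × (30.25 + 34.4569) / 4 = 169.82, which rounds up to 170. Then 170 / 0.9 = 188.9, so 189 per group and 378 in total, as stated.

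Nothing in the present point changes these numbers.

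**3. Illustration of why knowing the arm matters.** Assumptions, none of them from the document: no true effect, a normally distributed outcome, 189 analysed per arm, a two-sided t test at 5%, and deliberately one-sided exclusions. The common SD is √((30.25 + 33.4084) / 2) = 5.64.

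| Exclusion (simulated) | Type I error |
|---|---|
| None | 5.0% |
| 4 worst Chinese medicine outcomes, arm known | 8.3% |
| 8 worst outcomes regardless of arm | 4.8% |

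The first two rows use 20,000 simulated trials and the third 5,000.

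As a plausibility check, removing the 4 worst shifts the mean difference by about 0.28 CAT points. The standard error is 5.64 × √(2 / 189) = 0.58, so the shift is 0.28 / 0.58 = 0.48 standard errors. The two-sided rejection probability is then about Φ(−1.48) + Φ(−2.44) = 0.069 + 0.007 = 0.077. The smaller SD left after trimming accounts for the small remaining gap to 8.3%.

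Four patients are 4 / 189 = 2.1% of an arm. In this example the damage comes from knowing the arm: dropping 8 extreme values blindly leaves the error rate at its nominal level.

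**The case against.** The strongest reply has four parts.

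- **A contractor holding the list is ordinary, and the article speaks of units.** It does not say that the same individuals hold the code and decide exclusions, or that analysts decide exclusions at all. This stands, and so the point is that exclusions could be made with the arms known, not that they will be.
- **Blinded data review, sign-off before lock and internal firewalls usually sit in the full protocol, the analysis plan or the monitoring committee's charter.** This would answer a silence. Here the article makes a positive statement that the analysts are not blind. If a fuller document blinds them, the published sentence is wrong and needs correcting anyway.
- **The article also announces intention-to-treat analyses, which would show up selective mITT exclusions.** This is a useful check, but efficacy is assigned to the mITT set.
- **The main routes of bias stay closed.** Patients, care providers and assessors are blind. This stands: a reader might infer that most of the protection of double blinding is lost, and the document does not support that.

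Two further inferences are tempting and fail. A reader might attribute to unblinding a false-positive rate of 12.5% to 18% from choosing among the CAT time points and the permitted tests. That inflation comes from not fixing the primary analysis; a two-sided p-value is the same with arms labelled A and B, so blinding the analyst would not remove it. A reader might also list every data-dependent rule in the Statistical analysis section as open to abuse. The Kolmogorov-Smirnov rule only governs how variables are summarised, the t test and repeated-measures ANOVA are assigned by type of data, and the centre rule is triggered by a centre effect, not by knowledge of the arms. What remains is the mITT and rejection decisions.

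**Conclusion.** The concern holds in a limited form. The article says outright that the analysts are unblinded and places randomisation, data management, analysis planning and reporting with one contractor. It states no separation between code holders and analysts, and leaves exclusions from the efficacy set to judgement. Independence from data collection does not close that gap.

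The size of any bias cannot be derived from the document. The rise from 5% to about 8% shows the mechanism under assumed, deliberately selective exclusions and is not a forecast. Scenarios with unequal exclusion rates by arm, such as 15% against 5%, have no basis in the text either. The point warrants a change to the plan; it does not show that the trial is biased.

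**What to change.** Replace the blinding sentence under Randomization and blinding with one that counts the data analysts among those blind to allocation until three steps are complete:

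1. the statistical analysis plan is signed;
2. mITT and per-protocol membership and all rejections are fixed and documented at a blinded review;
3. the database is locked.

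Add that the allocation code stays in the central randomisation system until then, with access barred to the analysing statistician. The Trial status section reports recruitment complete and follow-up due to end in January 2020, so at that stage all three steps could still come before the analysis.

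The cost is wording and a change of access rights inside the contractor. If the person who generated the list is also the intended analyst, which the article does not say, those two roles would have to be divided. Any unblinded report for the Independent Data Monitoring Committee must be prepared apart from the trial analyst. Sample size and patient care are unaffected.
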